### 2.7. Gut Microbiome and Antibiotic Resistance Gene Analysis

For 16s rRNA sequencing for gut microbiome analysis, stool DNA will be isolated using QIAamp DNA Mini Kit (Qiagen, Germantown, MD, USA). A multiplex amplicon library converting the 16S rDNA gene V4 region will be generated from the DNA on the MiSeq machine (Illumina, San Diego, CA, USA). Microbial analysis will be performed using Qiime software with the Greengenes 99 database on the Nephele pipeline supported by the National Institutes of Health. The software will be used to calculate and generate alpha and beta diversities. For analysis of antibiotic resistance genes, tet(W), mel, msr(E), tet(M), erm(F), mef, and erm(B), which have been reported as genes related to antibiotic resistance [53], they will be examined by quantitative polymerase chain reaction using stool DNA.

### 2.8. Statistical Analysis

The primary and secondary endpoints and safety will be assessed in all patients completing 48 weeks of treatment. Then, patients without necessary exacerbation data for analysis or who withdrew consent before treatment will be excluded. For the primary endpoint, the asthma exacerbation rate at 48 weeks and its two-sided 95% confidence interval (CI) will be estimated with the normal approximation. The asthma exacerbation rate difference between pre- and post-treatment will also be tested binomially. For the clinical laboratory parameters and the diversity indices of the gut microbiome at pre-treatment and post-treatment as secondary endpoints, paired *t*-tests or McNemar’s tests will be used. The chi-squared test will be used to investigate the characteristics related to the frequency of asthma exacerbations. For other exploratory endpoints, height, weight, BMI, and tendency for an attenuation of the exacerbation rate at 24 weeks will be assessed by paired *t*-tests. Univariate analysis and multivariate analysis with a logistic regression model, adjusting BMI and body weight, will be performed to evaluate the relationships between the changes (improvement or no improvement in biomarker changes) and asthma exacerbation at 48 weeks.

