## 2. Materials and Methods

### 2.1. Study and Setting

The present study is a multi-center, open-label, prospective, single-arm intervention study. The duration of the intervention is 48 weeks. All patients with asthma are to be diagnosed by an expert pulmonary physician referring to the Global Initiative for Asthma (GINA) guidelines [39]. Briefly, the patients show asthma-related symptoms such as cough, sputum, shortness of breath, and/or wheezes, and clinical improvement, including the symptoms and/or forced expiratory volume in 1 s at more than 200 mL or 12% by treatment for asthma, including short-acting beta 2 agonists (SABAs) and inhaled corticosteroids. The body mass index (BMI) is calculated as the body mass divided by the square of the height (kg/m^2^). Obesity is defined as a BMI greater than 25 kg/m^2^, referring to the Japanese criterion [40]. In the present study, to focus on the effect of azithromycin on exacerbations in obesity-induced asthma patients, patients who have experienced one or more episodes of moderate or severe exacerbation in the previous year will be recruited according to the sample size calculation. Moderate exacerbations are defined as events that require a temporary or a permanent increase in the dose of inhaled corticosteroid, administration of antibiotics considering exacerbation of asthma-related symptoms, increased use of SABA for 2 or more consecutive days, and emergency visits related to asthma exacerbations without administration of systemic corticosteroids, referring to previous reports [36]. Severe exacerbations are defined as events that require administration of more than 10 mg of prednisolone for 3 consecutive days, hospitalization associated with the asthma exacerbation, and emergency visits related to asthma exacerbations with systemic corticosteroid administration, referring to previous reports [36]. The azithromycin regimen is 250 mg daily for 48 weeks, based on previous reports. Briefly, 48 weeks of azithromycin 500 mg, 3 times per week, showed a significant attenuating effect for exacerbations of asthma, but with 35% of patients experiencing diarrhea and 7% of patients stopping treatment due to severe adverse effects [36]. Another trial showed that 24 weeks of azithromycin 250 mg, 3 times per week, showed no significant effect on exacerbations of asthma compared to placebo [41]. In terms of adverse effects, the blood concentration of azithromycin 250 mg daily was significantly lower, with less adverse effects, including digestive disturbance and hearing disorder, compared to 500 mg, 3 times per week [42]. In addition, Japanese patients with non-tuberculosis mycobacteria who were administered azithromycin 250 mg daily for more than 1 year, which is approved by Japanese medical insurance, did not experience adverse effects other than skin rash in 3.2% [43,44]. According to these data, azithromycin 250 mg daily for 48 weeks was selected considering efficacy, safety, and standardization related to seasonal changes.

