### 2.5. Clinical Data to Be Collected, including Adverse Events

The present study consists of 7 visits: before intervention, at azithromycin initiation, 4 weeks later, 12 weeks later, 24 weeks later, 36 weeks later, and 48 weeks later. Informed consent will be obtained at visit 1 with recording of clinical information including treatment contexts for asthma, smoking index, exacerbation times in the previous year, and comorbidities. Physical measurements, electrocardiogram, and blood examination will be evaluated at all visits except for visit 1 to monitor adverse effects of azithromycin. Pulmonary function testing, FeNO, and asthma control tests are to be performed at visits 2, 5, and 7. Biomarker analyses of blood, including multiplex assay of cytokines and chemokines (Eve Technologies, Calgary, AB, Canada), short-chain fatty acids, and metabolomics analysis (Kyusyu Pro Search, Fukuoka, Japan) are to be performed at visit 2 and visit 7. Gut microbiome analysis with 16s rRNA Sequencing (Massachusetts Host-Microbiome Center at the Brigham and Women’s Hospital, Boston, MA, USA) will be performed at visit 1 and visit 7. In terms of adverse effects of azithromycin, if the participants have any symptoms, physical and laboratory abnormalities of grade 2 level associated with azithromycin, the dose will be reduced to 250 mg 3 times per week. If the participants have any symptoms, physical and laboratory abnormalities of grade 3 level associated with azithromycin, administration of azithromycin will be terminated immediately.

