### 2.6. Sample Size

A previous study reported that the incidence rate ratio of asthma exacerbations for azithromycin compared to placebo was approximately 0.6 [36], but the current participants have obesity, which is estimated to reduce the attenuation effect due to the pharmacological differences between lean and obese individuals [51,52]. Thus, we anticipate an incidence rate ratio of 0.9 with azithromycin and set the expected exacerbation rate after intervention at 90%, with the exacerbation rate before the intervention set at 100%. Based on the normal approximation of the binomial distribution with a significance level of 5% and power of 90%, 44 patients are required. Thus, the target sample size was set at 50 patients considering dropouts.

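### Safety as well as efficacy is analysed only in patients who complete 48 weeks of treatment, so patients stopped earlier for azithromycin-related grade 3 toxicity are left out of the safety results

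*Protocol article*

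**What the plan says.** The protocol article, section 2.8 (Statistical Analysis), gives one population for everything: "The primary and secondary endpoints and safety will be assessed in all patients completing 48 weeks of treatment". The sentence that follows adds that "patients without necessary exacerbation data for analysis or who withdrew consent before treatment will be excluded". The article names no other analysis set, for safety or for efficacy.

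Section 2.5 has two rules for toxicity attributed to the drug. At the lower level the patient continues on less drug: "grade 2 level associated with azithromycin, the dose will be reduced to 250 mg 3 times per week". At the higher level treatment ends: "grade 3 level associated with azithromycin, administration of azithromycin will be terminated immediately".

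Section 2.5 also schedules safety monitoring throughout: "Physical measurements, electrocardiogram, and blood examination will be evaluated at all visits except for visit 1 to monitor adverse effects of azithromycin". Table 1 agrees, with ECG and blood tests at visits 2 to 7.

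Section 2.6 requires 44 patients and sets a target of 50 to allow for dropouts. Section 2.4 defines the exacerbation rate as a proportion of analysed cases.

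**The concern.** A safety analysis should describe what happened to everyone exposed to the drug. Here membership of the safety set depends on not having been stopped early, and drug-related grade 3 toxicity is itself a mandatory reason for stopping. The set is therefore selected on the outcome it is meant to describe, and the loss falls on the more severe end: a grade 2 patient on the reduced dose can still complete, while a grade 3 patient stopped before week 48 cannot.

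This matters because section 2.1 chose the regimen partly on tolerability, citing an earlier trial of another regimen with "7% of patients stopping treatment due to severe adverse effects". A completer set cannot yield a comparable figure for this trial.

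The same restriction applies to the primary endpoint. The proportion with an exacerbation is estimated only among patients who stayed on drug for 48 weeks. In a single-arm trial no comparison group would reveal that selection.

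**Working it through.** **1. The rules side by side**

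- Section 2.8: the safety set is the patients who complete 48 weeks of treatment.
- Section 2.5: a related grade 3 abnormality ends treatment at once.
- Together: a patient stopped under section 2.5 before week 48 is outside the safety set. Monitoring data from visit 2 up to the stop would exist but not be analysed.
- Still inside the set: grade 2 patients who continue on the reduced dose to week 48, patients with a grade 3 event not attributed to azithromycin who stay on drug, and patients whose grade 3 abnormality is first found at visit 7.

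**2. The two sentences of section 2.8**

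A patient who withdrew before treatment can never complete 48 weeks of it. Excluding such patients after restricting to completers removes nobody. The exclusion has an effect only if the starting set is wider, so the sentences describe two different populations.

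**3. The plan's own figures**

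The step from 44 to 50 fits an allowance of 6/50 = 12%, since 44/(1 − 0.12) = 50. The 44 itself is not reproduced from the inputs in section 2.6: a one-sample normal approximation from 100% to 90% gives 15 with the null variance, or 95 (two-sided) with the alternative variance. That is a separate matter. Here 44 and 50 serve only as the plan's numbers of completers and enrolled patients.

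**4. Size for safety (illustration)**

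The 7% in section 2.1 belongs to 500 mg three times per week in another trial, so it is indicative only.

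- Expected stops among 50 treated: 50 × 0.07 = 3.5.
- Chance of at least one: 1 − 0.93^50 = 0.973.

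Stops for adverse events before week 48, with exact 95% confidence intervals:

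| Set | Stops | Proportion (95% CI) |
|---|---|---|
| Completers | 0/44 | 0% (0% to 8.0%) |
| All treated, 3 stops | 3/50 | 6% (1.3% to 16.5%) |
| All treated, 4 stops | 4/50 | 8% (2.2% to 19.2%) |
| All treated, 6 stops | 6/50 | 12% (4.5% to 24.3%) |

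The first row is fixed by the definition of the set and carries no information about tolerability. The last row assumes that every planned dropout is such a stop.

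**5. Size for efficacy (illustration)**

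Assume that all 6 planned dropouts are treated patients, and take 40 of 44 completers with an exacerbation, close to the planned 90%.

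- Completers: 40/44 = 90.9%.
- All treated, none of the 6 exacerbates: 40/50 = 80%.
- All treated, all 6 exacerbate: 46/50 = 92%.

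The completer figure could thus be lower than the all-treated one by 1.1 points, or higher by 10.9. At exactly 90% in completers with all 6 others exacerbating, the all-treated proportion is (44 × 0.90 + 6)/50 = 45.6/50 = 91.2%, a shift of 1.2 points. The 12-point span is simply 6/50, the share left out. It bounds what is unknown and does not measure bias.

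**The case against.** The strongest objection is that the completer reading is not settled. The exclusion of patients who withdrew before treatment suggests that the authors had a wider set in mind, and a condensed article may have merged two definitions. That is fair as to intent, but it does not repair the text. The operative sentence limits safety to completers in plain words and no wider safety set is named. Because the article fixes the population, this is not a detail left to an analysis plan that is not shown.

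Four stronger readings are tempting, and the document does not support them.

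- **All related grade 3 events disappear, or discontinuations will be reported as zero.** An abnormality first found at week 48 stays in the set. Section 2.8 fixes an analysis set and does not say how participant flow will be reported.
- **The efficacy estimate is too favourable.** The bounds run in both directions, and further in the unfavourable one. Neither direction nor size can be fixed from the article.
- **Patients will leave for worsening asthma or a change of therapy.** The article names neither as a reason. Section 2.1 allows corticosteroids and non-macrolide antibiotics for exacerbations during participation.
- **About 7% will stop here.** That rate comes from a different regimen. Section 2.1 expects fewer adverse effects with 250 mg daily and cites Japanese patients on that regimen with no adverse effect other than skin rash, in 3.2%.

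It is also true that the microbiome and blood biomarker comparisons need a visit 7 sample. For those, a set of patients assessed at week 48 is reasonable.

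**Conclusion.** The plan is wrong as written on the safety population. Followed literally, it leaves out patients stopped before week 48 for azithromycin-related grade 3 toxicity and makes adverse-event stops within the analysed set zero. This follows from sections 2.5 and 2.8 alone and needs no assumed rate; a single such stop is enough. The sizes are illustrative: 3.5 of 50 if another regimen's 7% applied, and at most 6 of 50 if every planned dropout were such a stop.

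The efficacy part is weaker. The primary proportion is conditioned on staying on drug, with bias of unknown direction. If the 6 planned dropouts are all treated patients, 90.9% in completers is compatible with 80% to 92% of all treated. That span is wider than the planned 10-point change from 100% to 90%, but its ends are extreme cases.

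Separately, the two sentences of section 2.8 that define the population do not fit together and must be reconciled.

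**What to change.** Rewrite the opening of section 2.8 to name separate sets:

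- **Safety:** all patients who take at least one dose, with all adverse events recorded whatever the reason for stopping.
- **Primary endpoint:** all treated patients, counting exacerbations to week 48 whether or not azithromycin is reduced or stopped. Prespecify a rule for patients lost before week 48, for example counting them as having an exacerbation, with best-case and worst-case bounds. This keeps the endpoint a proportion, as section 2.4 defines it.
- **Completers of 48 weeks:** a sensitivity analysis for the primary endpoint, and the set for secondary and biomarker comparisons that need a week-48 sample.

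The exclusion of patients who withdrew before treatment then fits as part of the definition of treated patients. The exclusion for missing exacerbation data should give way to the rule for patients lost.

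The dosing and stopping rules are untouched. The cost is wording, continued recording of exacerbations to week 48 in the few patients who stop drug, and possibly a slightly less favourable primary estimate.

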### 2.2. Inclusion Criteria

Patients diagnosed with asthma, age older than 20 years and less than 75 years, with BMI greater than 25 kg/m^2^ will be included. All patients must have experienced one or more episodes of moderate or severe exacerbations in the previous year. Written informed consent for participation in the present study will be obtained from all patients.

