### 2.4. Study Endpoints

The primary endpoint is reduction in the exacerbation rate after 48-week treatment with azithromycin compared to that before the intervention (Table 1). The asthma exacerbation rate is defined as the proportion of analyzed cases with asthma exacerbations after treatment. Secondary endpoints are differences in clinical and laboratory parameters between before and after azithromycin treatment, including the blood eosinophil ratio, eosinophil count, IgE, pulmonary functions such as vital capacity (VC), forced vital capacity (FVC), %VC, forced expiratory volume in one second (FEV_1_), FEV_1_%, and %FEV_1_, and weight, BMI, level of fractional exhaled nitric oxide (FeNO), and scores on the asthma control test. Other secondary endpoints are to clarify the characteristics of the frequency of asthma exacerbations in improving/non-improving patients, and the diversity indices of the gut microbiome including the Chao 1, Shannon, and Simpson indices. For other exploratory endpoints, height, weight, BMI, and the tendency for decreased exacerbations will be assessed at 24 weeks of azithromycin treatment. In addition, biomarkers including cytokines, chemokines, short-chain fatty acids, metabolomics, and species of the gut microbiome will be compared between before and after azithromycin treatment and examined for relationships between changes and exacerbation at 48 weeks. The effects of sex and age attenuating the effect of azithromycin on exacerbations will also be assessed, because sex and age have been shown to have great impacts on the incidence and pathophysiology of asthma and obesity [26,48,49,50].

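### The normal-approximation 95% CI fixed for the primary proportion under-covers around the planned 90% with 44 to 50 patients, and its upper limit can exceed 100%

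*Protocol article*

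**What the plan says.** Section 2.4 makes the primary endpoint a proportion of patients: "The asthma exacerbation rate is defined as the proportion of analyzed cases with asthma exacerbations after treatment". For that proportion at 48 weeks, section 2.8 says that the "two-sided 95% confidence interval (CI) will be estimated with the normal approximation". It then adds a test: "The asthma exacerbation rate difference between pre- and post-treatment will also be tested binomially".

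Section 2.6 gives the planning values. The authors "set the expected exacerbation rate after intervention at 90" per cent, "with the exacerbation rate before the intervention set at 100" per cent. The baseline figure follows from eligibility in section 2.2: "All patients must have experienced one or more episodes of moderate or severe exacerbations in the previous year". On size, section 2.6 states: "Based on the normal approximation of the binomial distribution with a significance level of 5% and power of 90%, 44 patients are required", and "the target sample size was set at 50 patients considering dropouts". Section 2.8 restricts the primary analysis to patients who complete 48 weeks, so the evaluable number should lie between about 44 and 50.

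**The concern.** The usual normal-approximation interval for a proportion (Wald) needs a reasonable number of both events and non-events. At the planned 90% there would be 0.10 × 44 = 4.4 to 0.10 × 50 = 5 non-events. In that region the standard error is estimated from very few patients. It shrinks when the observed rate happens to be high, and the interval stays symmetric although the parameter is bounded at 100%.

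This interval is the headline estimate of a single-arm trial. If it misses the true rate more often than the stated 5%, or reports an upper limit above 100%, the precision claimed for the main result is wrong. The article names the method, so this is not a detail left to an analysis plan.

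**Working it through.** **Inputs.** Planned post-treatment proportion 0.90 (section 2.6). Evaluable n of 44 (section 2.6), up to 50 if nobody drops out. Two-sided 95%, so z = 1.96 (section 2.8). The plan gives no figure for the interval, so there is none to reproduce. The 44 is taken as stated; it does not follow from 100% versus 90% by the usual normal-approximation formulas, but that is a separate matter and nothing below depends on it.

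**Step 1: the interval at exactly the planned rate.** Wald: p̂ ± 1.96 × √(p̂(1 − p̂)/n).
- n = 44: 0.90 ± 1.96 × √(0.09/44) = 0.90 ± 0.0886, giving 81.1% to 98.9%.
- n = 50: 0.90 ± 1.96 × √(0.09/50) = 0.90 ± 0.0832, giving 81.7% to 98.3%.

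Neither passes 100%.

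**Step 2: when the upper limit passes 100%.** With k ≥ 1 non-events, the upper limit exceeds 1 when k < 1.96² × p̂ = 3.84 × p̂.
- n = 44: k = 3 gives 3.84 × 41/44 = 3.58 > 3, so it overshoots; k = 4 gives 3.84 × 40/44 = 3.49 < 4, so it does not.
- n = 50: k = 3 gives 3.61 > 3; k = 4 gives 3.53 < 4.

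Overshoot therefore occurs with 41 to 43 of 44, or 47 to 49 of 50, exacerbating. The binomial probability of this is 33.7% (n = 44) or 24.5% (n = 50) at a true rate of 90%. At 95% it is 71.9% or 68.4%; at 80% it is 1.5% or 0.6%. If all 44 exacerbate (probability just under 1% at a true rate of 90%), the Wald interval is 100% to 100%.

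**Step 3: exact coverage.** Coverage at true rate p is the sum of Binomial(n, p) probabilities over all counts x whose interval contains p. At p = 0.90:
- n = 44: the interval contains 90% for x = 35 to 42. It lies wholly above 90% for x = 43 or 44 (5.7%) and wholly below for x ≤ 34 (1.0%). Coverage is 93.3%.
- n = 50: the interval contains 90% for x = 40 to 47. It lies wholly above for x = 48 to 50 (11.2%) and wholly below for x ≤ 39 (0.9%). Coverage is 87.9%.

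| Coverage | Wald | Wilson | Clopper-Pearson |
|---|---|---|---|
| n = 44, p = 0.90 | 93.3% | 96.2% | 98.0% |
| n = 50, p = 0.90 | 87.9% | 97.0% | 97.0% |
| n = 44, mean over p = 0.85 to 0.95 | 90.3% | 95.6% | 97.6% |
| n = 50, mean over p = 0.85 to 0.95 | 90.6% | 95.4% | 97.3% |
| n = 44, minimum over that range | 79.5% | 93.4% | 95.2% |
| n = 50, minimum over that range | 80.0% | 93.3% | 95.1% |

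Wald coverage is erratic in n: at p = 0.90 it runs from 86.4% (n = 48) to 95.0% (n = 47) over n = 40 to 50.

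**Step 4: lower true rates.** Wald coverage at p = 0.80 is 93.6% (n = 44) or 93.8% (n = 50). At p = 0.60 it is 95.5% or 94.1%.

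**Step 5: what a result would look like.**

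| Observed | Wald | Wilson | Clopper-Pearson |
|---|---|---|---|
| 40/44 | 82.4% to 99.4% | 78.8% to 96.4% | 78.3% to 97.5% |
| 41/44 | 85.7% to 100.6% | 81.8% to 97.7% | 81.3% to 98.6% |
| 42/44 | 89.3% to 101.6% | 84.9% to 98.7% | 84.5% to 99.4% |
| 44/44 | 100% to 100% | 92.0% to 100% | 92.0% to 100% |

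**The case against.** **The loss may be small.** At the planned evaluable n of 44 and a true rate of exactly 90%, coverage falls short by 1.7 points, and for n = 45 to 47 it is 93.6% to 95.0%. The 87.9% needs all 50 patients to complete. Section 2.6 also deliberately weakens the anticipated effect, from a ratio of about 0.6 in the earlier azithromycin trial to 0.9, so the true rate may be well below 90%. All of this is correct. But a favourable n such as 47 sits next to an unfavourable one such as 48, and nobody can choose the final n or the true rate. The average over 85% to 95% is the fairer summary, and there the interval misses nearly twice as often as stated.

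**A reader might infer that the interval overshoots 100% at the plan's own value.** It does not: at an observed 90% it runs from about 81% to 99%. The 100% in section 2.6 is the pre-treatment value, not the expected result. Overshoot is a possible outcome, not a certain one.

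**A reader might also infer that the interval contradicts the binomial test.** The text does not support that. Section 2.8 gives an interval for one proportion and, as a further output, a test of the pre-post difference. It does not say that the interval decides the primary question, or that the test is exact. Section 2.6 uses a normal approximation for the sample size, so an approximate test is equally possible, and a Wald test with the estimated variance would agree with the Wald interval by construction. Only if an exact test against 100% is meant would one exacerbation-free patient reject while the Wald interval still reaches 100%, at 41 to 43 of 44. Even then the root cause is a comparator fixed at 100% by eligibility, which a better interval leaves in place.

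**Conclusion.** The concern holds as a modest but clear fault in a stated method. Around the planned 90% with 44 to 50 evaluable patients, the nominal 95% interval covers about 90% on average. The misses are lopsided: the interval falls wholly above the true rate far more often than wholly below it, so it tends to place the exacerbation rate too high. The chance of an upper limit above 100% is about one in three (n = 44) or one in four (n = 50) if the true rate is 90%.

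This rests on three assumptions: that the normal approximation means the Wald interval, its usual sense; that 44 to 50 patients are analysed; and that the true rate is near the planned one. The point estimate and the sample size are unaffected. The change should be made because it is essentially free, not because the trial depends on it.

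**What to change.** In section 2.8, replace the normal-approximation interval for the 48-week exacerbation proportion with a two-sided 95% Wilson score interval, or Clopper-Pearson if guaranteed coverage is preferred. Both stay within 0% to 100% and keep a sensible width when all patients exacerbate.

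The cost is one line of text. Limits may be slightly wider: at 41/44 the width is 14.9 points for Wald, 15.9 for Wilson and 17.2 for Clopper-Pearson. Clopper-Pearson is somewhat conservative here (about 97% to 98% coverage).

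It would help to state in the same sentence whether the binomial test is exact or approximate, so that readers know whether test and interval can differ. The 100% pre-treatment value built in by the inclusion criterion needs its own treatment.

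### The only test named for comparing improving with non-improving patients is chi-squared, so any numeric characteristic would have to be cut into categories, at a cost in power (minor)

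*Protocol article*

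**What the plan says.** Section 2.4 sets the endpoint: "Other secondary endpoints are to clarify the characteristics of the frequency of asthma exacerbations in improving/non-improving patients". It does not define improving. It does define the exacerbation rate as a binary quantity: "The asthma exacerbation rate is defined as the proportion of analyzed cases with asthma exacerbations after treatment".

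Section 2.8 gives the method for this endpoint in one sentence: "The chi-squared test will be used to investigate the characteristics related to the frequency of asthma exacerbations". It lists no characteristics, cut-points or chi-squared variant.

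The other methods in section 2.8 serve other questions. Paired t-tests or McNemar's tests are for before/after change. Logistic regression is for the exploratory link between biomarker changes, described there as improvement or no improvement, and exacerbation at 48 weeks. No full-scale method is assigned to the improver comparison.

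On numbers, section 2.6 has "set the expected exacerbation rate after intervention at 90%, with the exacerbation rate before the intervention set at 100" (per cent), requires 44 patients and recruits 50. Section 2.8 restricts the analysis to completers: "The primary and secondary endpoints and safety will be assessed in all patients completing 48 weeks of treatment". About 44 to 50 patients would therefore be analysed.

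**The concern.** A chi-squared test works on categories. Sections 2.4 and 2.5 collect mostly numeric or ordinal measures: age, weight, BMI, smoking index, eosinophils, IgE, lung function, FeNO, asthma control test score and the number of exacerbations in the previous year. If any of these is to be examined as a characteristic of improvers with the test named, it must first be cut. Cutting discards information, and cut-points that are not fixed in advance can be chosen after the data are seen.

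The endpoint is meant to show which obese patients with asthma improve, in a sample of about 44, where little information can be spared. If improvers are few, the cells of the table also become too small for the chi-squared approximation to be trusted.

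**Working it through.** **Inputs.** From the article: 44 patients required, 50 targeted, planned post-treatment exacerbation rate 90%. Assumed, because the article does not give them: a normally distributed characteristic, a difference of 0.5 to 1.25 SD between groups, the cut-point, the improver share, and a two-sided 5% level. The article states no power or error rate for this analysis, so there is no figure of its own to reproduce. The 44 belongs to the primary endpoint and is taken as given; how it was derived does not bear on this point.

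**Step 1. Power with fixed group sizes.** Simulation, 44 patients, median split, uncorrected Pearson chi-squared:

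| Improving / not | Difference | t-test | Wilcoxon | Chi-squared | Loss, t-test minus chi-squared |
|---|---|---|---|---|---|
| 22 / 22 | 0.8 SD | 74% | 72% | 49% | 25 points |
| 13 / 31 | 0.8 SD | 66% | 63% | 47% | 19 points |
| 9 / 35 | 1.0 SD | 74% | 70% | 40% | 34 points |
| 5 / 39 | 1.2 SD | 70% | 63% | 47% | 23 points |

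Repeat runs move these figures by 1 to 2 points. All four rows use a median split and large effects.

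**Step 2. Power over a wider range.** Here the number of improvers varies at random around its expected share (44 patients).

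- Improver share 10%, median split, t-test against chi-squared: a 5-point loss at 0.5 SD; 33% against 19% at 0.8 SD (14 points); 46% against 26% at 1.0 SD (20); 63% against 36% at 1.25 SD (27).
- Improver share 10%, cut at 70/30 or 80/20: the loss is -2 to 7 points.
- Improver share 30% to 50%: the loss is 8 to 31 points.

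A well-placed cut can cost nothing against the rank test. With 50 patients, 10% improvers, 0.8 SD and a 70/30 cut, power is 36% (t-test), 32% (Wilcoxon) and 34.5% (chi-squared).

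**Step 3. Cell counts if improving means exacerbation-free.** Expected improvers: 44 × 0.10 = 4.4, or 50 × 0.10 = 5. A median split halves this, so two of the four cells have expected counts of 2.2 (or 2.5), below the usual threshold of 5.

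**Step 4. Error rate in that case.** Take 44 patients, a median split and uncorrected Pearson. If all m improvers fall on one side of the median, chi-squared = 44 × (22m)² / [m × (44 − m) × 22 × 22], against a critical value of 3.84.

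- m = 3: 44 × 66² / (3 × 41 × 484) = 3.22. Rejection is impossible, so the error is 0%. The same holds for smaller m.
- m = 4: 44 × 88² / (4 × 40 × 484) = 4.40, p = 0.036. The true probability of such a split is 2 × C(22,4)/C(44,4) = 2 × 7315/135751 = 10.8%.
- m = 5: 2 × C(22,5)/C(44,5) = 2 × 26334/1086008 = 4.9%.
- m = 6: 2.1%. m = 7: 9.5%.

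Averaging over m with binomial weights (44 patients, 10%), the main terms are 0.201 × 10.8% + 0.178 × 4.9% + 0.129 × 2.1% + 0.078 × 9.5% = 4.1%. The rarer values of m bring this to about 4.3%. The probability of 3 or fewer improvers, where the test cannot reject, is about 35%.

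With a continuity correction, m = 4 gives 44 × (88 − 22)² / 77440 = 2.475, p = 0.116, and m = 5 gives 44 × (110 − 22)² / (5 × 39 × 484) = 3.61. Neither can reach 5%. The probability of 5 or fewer improvers is about 73%. The article does not say that this correction will be used.

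**The case against.** The strongest reply is that the article never says numeric characteristics will go into this test. Eosinophils, IgE, FeNO, lung function, weight, BMI and the asthma control test score appear in section 2.4 as before/after endpoints with their own paired tests. Visit 1 also collects categorical items such as comorbidities and asthma treatment, for which a contingency-table test is natural. The list of characteristics, the cut-points, the definition of improving, the chi-squared variant and any small-cell fallback are details that a condensed article may leave to the full protocol or SAP. This stands: none of those gaps is counted as a fault here. What remains is that section 2.8 makes a positive choice of one test for the whole endpoint, and that choice does not fit most of the data collected.

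Two stronger readings are tempting.

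- A reader might infer that the plan loses some 20 to 35 power points. The article fixes no effect size, cut or improver share. At the planned 10% exacerbation-free, a loss of 20 points or more needs both a median split and an effect of at least 1.0 SD.
- A reader might infer that the test has the wrong error rate at the planned 90%. Averaged over the number of improvers, uncorrected Pearson is close to nominal: 4.3% to 5.8% with 44 patients across the cuts examined. The 10.8% applies only when exactly 4 patients are exacerbation-free.

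The small-cell argument also depends on equating improving with exacerbation-free. Patients enter with one or more exacerbations in the previous year, so improving could instead mean a fall in their number, and the 90% would then not set the split.

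**Conclusion.** The point holds as a minor one. The single test named for this endpoint can use numeric characteristics only after they are cut. With about 44 patients that can cost from almost nothing to about 30 points of power against a full-scale test; the most unfavourable fixed split examined, 9/35 at 1.0 SD, reached 34. The range rests on assumed normal data and on assumed effects, cuts and improver shares. The loss does not need improvers to be rare, since it also appears at 22/22 and 13/31.

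The small-cell concern is conditional. If improving means exacerbation-free, the conditional error of uncorrected Pearson on a median split jumps between 0% and 10.8% with the observed count. That makes a single p-value hard to trust, but it is not a systematic inflation of the error rate.

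The analysis is secondary and descriptive, and the article attaches no decision to it.

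**What to change.** In section 2.8, replace the chi-squared sentence. Compare continuous and ordinal characteristics between improving and non-improving patients on their full scale, with a Wilcoxon rank-sum test, or a t-test after log transformation for skewed markers, and report each difference with a 95% CI. Keep contingency-table tests for characteristics that are truly categorical, such as sex or comorbidity, and use an exact test where expected counts fall below 5.

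The cost is one or two sentences, with no new data, visits or patients. Results would appear as mean or median differences rather than percentages above a cut. The exact test is conservative (Fisher's true error is 0.9% to 2.4% at the planned rate) and recovers no power; it only guards against small cells. If only 4 to 5 patients improve, power stays low under any test: 33% for the t-test at 0.8 SD with 44 patients.
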